**Indicators of implementation of the intervention**

Finally, we will measure the good implementation of the intervention by looking at:

1. Health care utilisation
2. Out-of-pocket expenditures
3. Health shocks
4. Patient satisfaction

**Participant timeline {13}**

A schematic diagram is presented in Figure 1.

Figure 1: Schedule of enrolment, interventions, and assessments

**Sample size {14}**

The baseline study has recruited 1,508 unmarried girls and young women engaging in transactional (753) and commercial (755) sex in Yaoundé, Cameroon. Currently, 1,147 participants have been randomised via participatory randomisation, 568 participants allocated to the control arm and 579 allocated to the treatment arm. To maximise statistical power, STI-positive participants receive free treatment at baseline to start the trial with an STI-free cohort. Participants will also receive free treatment at midline to allow for the possibility to observe more than one STI per participant over the trial period. Free treatment will also be provided at endline for ethical reasons. Assuming that 20% of participants will get at least one STI over the trial period, this sample size is sufficient to show a decrease of 30% (6 percentage points) in the incidence of any STI in the treatment group assuming 80% power and a significance level of 5%. To conduct analysis separately among the sub-samples of those engaging in commercial and transactional sex, the MDE is a ~40% reduction (8.3 percentage points) in STI incidence. Assuming an HIV incidence of 4% over the trial period, the sample size would allow the detection of a decrease of 65% in HIV incidence (2.6 percentage points).

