**Discussion**

POWER aims to advance understanding of the structural drivers of STIs and HIV by analysing the role of a recently identified and under-researched factor: economic shocks. This study is the first to provide evidence of the effectiveness and value for money of a formal shock-coping strategy, health insurance, to prevent STIs and HIV in Africa using an RCT. Hence, POWER will generate robust and rigorous information on the causal mechanisms that determine STI and HIV acquisition in vulnerable women in Cameroon. This information will be a vital contribution to support the pressing need to achieve universal health coverage and to identify novel cost-effective interventions to address the burden of HIV in Africa. By contributing to both debates, the research project will enhance the efficiency of UK and international aid and has the strong potential to have a long-lasting impact on shaping the research agenda on HIV.

A study of this size and complexity does have several limitations and risks. Primarily, there may be participant loss since we already observe an attrition of 23% between recruitment and randomisation. In addition, issues in the implementation of the intervention are likely to be frequent given the lack of experience in implementing health insurance projects of this size in Cameroon. Additionally, issues inherent to the quality of care could lead to an under-utilisation of healthcare services, which would prevent the evaluation of the effect of the intervention of the primary and secondary outcomes.

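### The 80% power claims need about 1,210 to 1,230 women with outcomes; 1,147 were randomised, giving about 77% to 78% with full follow-up and less with any loss

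*Protocol*

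**What the plan says.** The Sample size {14} section of the protocol first gives 1,508 women recruited at baseline (753 transactional, 755 commercial). It continues: "Currently, 1,147 participants have been randomised via participatory randomisation", with 568 in control and 579 in treatment. Three power claims follow, at 80% power and a 5% significance level.

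- **Any STI.** "Assuming that 20% of participants will get at least one STI over the trial period", the section concludes that "this sample size is sufficient to show a decrease of 30% (6 percentage points) in the incidence of any STI in the treatment group".
- **Each stratum.** For commercial and transactional sex analysed separately, "the MDE is a ~40% reduction (8.3 percentage points) in STI incidence".
- **HIV.** With control risk put at 4%, the claim made is that "the sample size would allow the detection of a decrease of 65% in HIV incidence (2.6 percentage points").

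The section does not say which of the two totals was used, whether the test is two-sided, or what loss to follow-up was assumed. In the Discussion, participant loss is named as a possible limitation, on the ground that "we already observe an attrition of 23% between recruitment and randomisation". The Trial status section says recruitment has ended.

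**The concern.** The section prints two totals and one set of detectable effects, and those effects do not follow from either total. The number that matters is the one randomised, and it is smaller than the claims require.

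STI acquisition and HIV status are the primary outcomes, and separate analyses by stratum are planned in Statistical methods {20a}. A null or borderline result will be read against the stated 80% power for a 30% reduction. If the real figure is lower, a missed effect of that size is more likely than the protocol tells its reader.

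**Working it through.** **Inputs, all from Sample size {14}.** Control risk of any STI is 20%, with effects of 6 points overall (14%) and 8.3 points per stratum (11.7%). Control risk of HIV is 4%, with an effect of 2.6 points (1.4%). Power is 80%, alpha 5%, and the arms are 568 and 579. Two-sided testing is my assumption, tested in step 4. The stratum sizes after randomisation are not given, so I assume an even split of 1,147, or about 287 per arm per stratum.

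**Step 1. Can the stated effects be reproduced?** Solving for the detectable difference at 80% power (pooled-variance test, two-sided):

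| Women with outcomes | Any STI | Per stratum | HIV |
|---|---|---|---|
| Stated | 6 | 8.3 | 2.6 |
| 1,147 | 6.19 | 8.50 | 2.66 |
| 1,508 | 5.45 | 7.51 | 2.38 |
| 1,206 | 6.05 | 8.32 | 2.61 |

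Neither printed total returns the stated set. A total of about 1,206, which is 0.80 × 1,508, comes close on all three.

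**Step 2. Number needed.** Per arm, with p̄ the mean of the two risks:

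n = [1.960 √(2p̄(1−p̄)) + 0.842 √(p1(1−p1) + p2(1−p2))]² / (p1−p2)²

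- Any STI: (1.0412 + 0.4457)² / 0.06² = 2.2107 / 0.0036 = 614.1, so 615 per arm and 1,230 in all.
- Stratum: (1.0123 + 0.4319)² / 0.083² = 2.0856 / 0.006889 = 302.7, so 303 per arm, 606 per stratum and 1,212 for both.
- HIV: (0.4493 + 0.1923)² / 0.026² = 0.4116 / 0.000676 = 608.9, so 609 per arm and 1,218 in all.

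The any-STI requirement exceeds 1,147 by 83 women, or 7%.

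**Step 3. Power at the randomised number, no loss.** Power = Φ[(p1 − p2 − 1.960 SE0) / SE1], where SE0 uses the pooled risk and SE1 the separate risks.

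- Any STI: SE0 = 0.02217, SE1 = 0.02213, so Φ(0.748) = 77.3%.
- HIV: SE0 = 0.00955, SE1 = 0.00956, so Φ(0.761) = 77.7%.
- Stratum, about 287 per arm: 77.8%.

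**Step 4. Other formulas.** For any STI at 568/579, unpooled variance gives 77.4% and arcsine 77.5%. A continuity correction raises the need to 1,294. For HIV, unpooled gives 77.6% and arcsine 80.0%. A one-sided 5% test would give 85.6% for any STI, but its detectable differences at 1,147 would be 5.54, 7.63 and 2.42 points. These are not the stated figures, so the protocol's numbers look two-sided.

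**Step 5. Loss after randomisation.** The protocol gives no rate. The 10% and 20% rows are assumptions, applied equally to both arms.

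| Loss | Women left | Any-STI power | Any STI | Per stratum | HIV |
|---|---|---|---|---|---|
| 0% | 1,147 | 77% | 6.2 | 8.5 | 2.7 |
| 10% | 1,032 | 73% | 6.5 | 8.9 | 2.8 |
| 20% | 918 | 68% | 6.9 | 9.4 | 2.9 |

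The last three columns are detectable differences in points at 80% power.

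**The case against.** The strongest reply is that, on the documents alone, the gap is close to rounding: 6.2 against 6 points, 8.5 against 8.3 (itself glossed as roughly 40%), and 2.7 against 2.6. The planning risks are round guesses. With 21% control risk, a 30% reduction has about 80% power at 1,147; with 18.5%, a 6-point fall does. Statistical methods {20a} also plans regression accounting for baseline differences. If covariates explained about 7% of outcome variance, 80% would be restored with full follow-up.

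Much of this stands, and it limits the size of the point. It does not rescue the statement. The protocol commits to 20% and 4%, claims no precision gain from adjustment, and the any-STI figure misses 80% under every two-sided formula tried. The HIV claim is less clear, since arcsine supports it at 1,147 with no loss.

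Three stronger readings are tempting, but the documents do not support them.

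- **That power is really 65% to 73%.** Those values rest on post-randomisation loss rates that appear nowhere in the protocol. The Discussion says loss may occur, and its 23% precedes randomisation. Section {18b} describes retention measures, including later insurance for control women who complete follow-up.
- **That 1,508 is passed off as the trial sample.** The section separates women recruited to baseline from women randomised, and gives the arm counts.
- **That the effects were computed from 1,508 less 20% loss and never updated.** The match with 1,206 suggests it, but the protocol does not say so.

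**Conclusion.** The point holds, at modest size. The three stated effects need about 1,230, 1,212 and 1,218 women with outcomes, and 1,147 were randomised with recruitment closed. With complete follow-up, two-sided power is about 77% for any STI and about 78% per stratum and for HIV (80% for HIV under arcsine), against the stated 80%. Any loss after randomisation widens the gap, and the section states no allowance for it.

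This rests on two-sided testing at 5%, the protocol's own control risks, an even split of the randomised women between strata, and no precision gain from covariates. It is an error in a stated figure. It is not evidence that the trial is badly underpowered, and no decision on design or conduct turns on it.

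**What to change.** In Sample size {14}, say that the power statement refers to the 1,147 women randomised and that the test is two-sided, if that is intended. Restate the differences detectable with 80% power and full follow-up as about 6.2 points (31%) for any STI, 8.5 points (about 42%) per stratum, and 2.7 points (67%) for HIV. Use the actual randomised stratum counts in place of an even split.

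Add the same figures under a retention rate that is explicitly labelled an assumption, such as the 10% and 20% loss rows in the working, with the matching any-STI power.

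The cost is wording only. The stated figures become slightly less favourable, and nothing in the design, conduct or analysis changes.

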**Recruitment {15}**

Participants are recruited using RDS, a chain-referral recruitment method that allows for unbiased population estimates. Initial participants (seeds) were identified by the CBOs. Seeds, and all subsequent participants, were required to recruit up to three of their friends that met the eligibility criteria. A motivation of 500 FCFA (=0.64 GBP, in 2022 prices) was given to participants for each (up to three) participant recruited. Study staff, alongside peer leaders/mobilisers, will follow participant recruitment, calling participants who have not recruited anyone onto the study to encourage them to do so.

**Assignment of interventions: allocation**

**Sequence generation {16a}**

Randomisation is conducted at the individual level using a participatory approach with a target of a 1:1 ratio to treatment or control group stratified by engagement in commercial or transactional sex. Formative research, conducted before randomisation, found that participatory randomisation was the preferred method of randomisation by the target population. Participatory randomisation was deemed fairer and more transparent than computer-based randomisation.

**Concealment mechanism {16b}**

A protocol has been developed to minimise the opportunity to fix randomisation so participants all receive the treatment. Two balls, one orange (allocating participants to the treatment group) and one white (allocating participants to the control group) are placed in a long black opaque bag. Participants are required to draw one ball out of the bag and cannot see inside. Hence, participant allocation to the treatment and control arm is known by the participants, the enumerators and supervisors at the time of the draw.

**Implementation {16c}**

Before the draw is conducted, the enumerators will take the participant through the informed consent process, explain the randomisation process and define the meaning of the two different coloured balls. After the participant consents to take part in the study and before the randomisation process begins participants are asked several questions to ensure that they understand how randomisation will be conducted.

All participants who give consent for participation and who fulfil the inclusion criteria will be randomised. Randomisation is conducted with a participant in a private room by two enumerators under the supervision of a site supervisor. No draw can occur in the absence of those three witnesses. This is to ensure that the assignment of participants to the treatment or control group is conducted fairly and transparently. One enumerator leads the randomisation whilst the other completes the participant's responses in an ODK-based survey. Firstly, the enumerator will ask the participant to feel the bag to demonstrate the bag is empty and that the draw is not rigged by the POWER team. Then the enumerator will place one orange and one white ball in the empty bag in front of the participant. The participant will then place then hand and arm, up to their elbow, in the bag. A drawstring is tightened underneath the participant's elbow so they are unable to see inside the bag. The enumerator holding the drawstring is standing up by the participant to ensure that the participant cannot see inside the bag. The participant must then shuffle the balls around in their hand inside the bag. When the participant is ready to draw, they must notify the enumerator to loosen the drawstring. Participants only have one chance to draw a ball from the bag. When the draw is complete, and participants have been allocated to their treatment group, treatment participants are requested to re-consent to the study after receiving a description of the insurance product. If treatment participants chose to remain in the study, they will receive the health insurance product. If not, they will withdraw their participation from the study.

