**Plans to promote participant retention and complete follow-up {18b}**

**Participant retention**

Participants are not incentivised or coerced to participate in the study. During the informed consent process, the benefits of the study are outlined in detail to encourage participant retention. The primary benefit highlighted is the possibility that this project will contribute to the proposal of public policy intervention to improve the quality of life of young women who engage in transactional and commercial sex.

In addition, all participants receive compensation for their time and travel costs. Participants are compensated 2000 FCFA (2.57 GBP, in 2022 prices) for their time and travel when responding to on-site questionnaires. This compensation will act to reduce any barriers to participant participation (e.g., transport fees). In addition, they receive free STI and HIV testing on-site at baseline, midline and endline. Those with a positive STI test will be offered free treatment (regardless of group status). This will be covered by POWER directly and not by the health insurance package for those in the treatment group. HIV-positive participants will be referred to initiate antiretroviral treatment.

Participants receive airtime to reply to weekly SMS diary surveys and an additional financial incentive. To achieve higher retention and completion rates a compensation for their time of 1000 FCA francs (1.28 GBP, in 2022 prices) is offered to all participants with a completion rate of diaries superior to 90% over the last 30 days.

To retain participants in the control group, the project offers the same health insurance product to all eligible control group participants at the end of the data collection period. To be eligible for this health insurance product, control participants must remain in the study by completing all follow-up surveys and responding to the SMS survey.

Further to the potential benefits of the study, study site staff are also responsible for supporting the development and implementation of procedures to support the retention of participants, using their knowledge of the context. Peer leaders (at HF) and mobilisers (at RENATA), CBO staff members who work closely with the target group, will use their extensive experience and networks to encourage participants to continue participation in the study. The study Advisory Group will also be consulted about the retention strategies of participants.

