**Participant withdrawal**

Participation is voluntary and participants can withdraw at any time, without giving reasons, by notifying a project staff member. Participant information already collected will be suppressed from the dataset. For control participants, withdrawal from the study means that participants are no longer entitled to the health insurance product provided at the end of the study. Withdrawal of participants on the treatment arm of the study will not impact any services or medical treatment they receive or any relationships they have with those treating them outside of the POWER project. However, any treatment or services that the participant and/or their nominated economic dependents receive will no longer be covered by health insurance provided by the POWER project. If the participant chooses to withdraw, they must choose to either stop ongoing treatments for themselves and their economic dependents or find an alternative means of paying for them.

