**Statistical methods**

**Statistical methods for primary and secondary outcomes {20a}**

All statistical analyses will be conducted using STATA. Descriptive statistics will first be used to summarise participant characteristics between the study groups. To investigate the effect of health insurance on primary and secondary outcomes, the analysis will use an intention-to-treat (ITT) approach where participants will be analysed in their allocated randomised study group. If there are non-compliers, i.e., participants and economic dependents who do not use the health insurance product when sick, we will also estimate the local average treatment effect (LATE). To investigate the effect of health insurance on primary and secondary outcomes, baseline characteristics will be compared for the treatment and control groups and determine whether there is differential attrition between the two groups. Outcomes for the treatment versus the control group will then be compared accounting for any baseline or attrition differences using ordinary least squared. The analysis will be conducted for all women and then separately for women engaging in transactional and commercial sex separately. A causal mediation analysis will be conducted to assess how much of the effect of health insurance on STI and HIV acquisition operates through risky sexual behaviours.

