**Methods in analysis to handle protocol non-adherence and any statistical methods to handle missing data {20c}**

Non-compliance issues will be investigated by estimating the local average treatment effect (LATE).

In addition, we will enquire about cases of STIs that were untreated at baseline and will also provide evidence of the impact of the intervention by removing participants who test positive at midline and endline because they did not take their treatment at baseline.

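### Only women drawn to treatment are asked to re-consent, decliners leave the study and withdrawn data are suppressed, so any refusal or withdrawal breaks the stated intention-to-treat analysis

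*Protocol*

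**What the plan says.** Four parts of the protocol bear on this.

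- **Implementation {16c}.** Consent comes before the draw: "All participants who give consent for participation and who fulfil the inclusion criteria will be randomised". The meaning of the two ball colours is also explained beforehand. Once the arm is known, "treatment participants are requested to re-consent to the study after receiving a description of the insurance product". Those who agree receive the insurance. For the others: "If not, they will withdraw their participation from the study". No matching step is described for controls.
- **Participant withdrawal.** For anyone who withdraws, in either arm: "Participant information already collected will be suppressed from the dataset".
- **Statistical methods {20a}.** The protocol states that "the analysis will use an intention-to-treat (ITT) approach where participants will be analysed in their allocated randomised study group". The analysts will also compare baseline characteristics, "determine whether there is differential attrition between the two groups", and adjust for differences by ordinary least squares. Non-compliers, described there as people who do not use the insurance when sick, are handled by a local average treatment effect (LATE); section {20c} repeats this.
- **Participant retention.** To receive the insurance after the trial, "control participants must remain in the study by completing all follow-up surveys and responding to the SMS survey".

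Sample size {14} gives 568 women allocated to control and 579 to treatment. It does not say whether the 579 were counted before or after re-consent.

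**The concern.** Implementation {16c} treats two decisions as one: declining the insurance and leaving follow-up. Nothing in the protocol lets a woman refuse the product and stay in the study. A woman who draws orange and refuses is removed after randomisation because of her allocation. A comparable woman who draws white meets no such step and stays in the control group. Intention-to-treat exists to prevent exactly this kind of exclusion.

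The suppression rule makes it harder to detect or correct, because the baseline data that would show who left are removed with them. The published result could then be labelled intention-to-treat although the protocol's own rules had taken randomised women out of one arm. A statistical analysis plan cannot cure this: it cannot restore follow-up that was never collected or data that have been suppressed.

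**Working it through.** **The rules side by side.** Suppose one woman draws treatment and declines.

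1. Under {16c} she has been randomised but leaves the study, so she has no midline or endline outcome.
2. Under the withdrawal rule her baseline information is suppressed.
3. Under {20a} she must be analysed in the treatment group. Steps 1 and 2 prevent this.
4. The baseline comparison of leavers and the least-squares adjustment need her covariates, which step 2 removes. At most, the fact that she left may survive in the draw record.
5. A LATE estimate divides the intention-to-treat difference by the difference in take-up, both taken over everyone randomised. A decliner is a never-taker who must stay in the treatment arm for that ratio to be valid. LATE therefore inherits the problem.

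**The protocol's target, as a yardstick.** Sample size {14} assumes 20% risk of any STI, a fall of 6 points to 14%, 80% power and a 5% significance level (two-sided assumed). With the pooled-variance formula:

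n per arm = [1.96·√(2·0.17·0.83) + 0.8416·√(0.20·0.80 + 0.14·0.86)]² / 0.06² = 615, or 1,230 in total.

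With the 568 and 579 women randomised, power is 77.3% and the detectable difference is 6.19 points. That rounds to the stated 6, so it serves as the yardstick. The concern does not rest on this small shortfall.

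**Size of the bias.** Take a true null effect and 20% risk in both arms. Let f be the share of the treatment arm that declines and r their STI risk. The documents give neither, so both are assumptions.

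Shift in treatment-arm rate = (0.20 − f·r)/(1 − f) − 0.20 = f·(0.20 − r)/(1 − f)

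| f (of 579) | r = 10% | r = 30% | r = 40% | Type I error |
|---|---|---|---|---|
| 1% (about 6) | +0.10 points | −0.10 | −0.20 | 5.0% to 5.1% |
| 5% (about 29) | +0.53 | −0.53 | −1.05 | 5.6% to 7.3% |
| 10% (about 58) | +1.11 | −1.11 | −2.22 | 7.4% to 15.5% |

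Example: f = 10%, r = 40% gives 0.10 × (−0.20)/0.90 = −0.0222, which is 2.22/6 = 37% of the target difference. A negative shift makes the insurance look protective; a positive one makes it look harmful. The type I error uses a two-sided 5% normal test with 568 controls and 579·(1 − f) treated women. The power cost is minor: 77.3% falls to 76.1% at f = 5% and 74.9% at f = 10%.

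**What the allocation counts can show.** A split of 579 to 568 fits 1:1 (exact p = 0.77). If 579 was counted after re-consent, about 57 refusals would still be compatible with a fair draw: 579 + 57 = 636 against 568 gives z = (636 − 602)/√(1,204/4) = 1.96, and 57/636 is about 9%. The split therefore neither shows refusals nor rules them out.

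**Width of worst-case bounds.** If a share f of the treatment arm has no outcome and the rate among those retained is p, the arm's rate lies between (1 − f)·p and (1 − f)·p + f. The width is f. With p = 20%, the interval is 19.8% to 20.8% at f = 1%, and 18% to 28% at f = 10%.

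**The case against.** A reader might infer that the intention-to-treat comparison cannot be done at all and that no trace of the removed women remains. The documents do not support either statement.

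- **No refusal is reported.** With no refusals and no withdrawals, the comparison is intact. Refusal may be rare: willingness to accept the intervention was explored beforehand, consent and an explanation of the ball colours precede the draw, and the insurance is free and covers up to six dependents. This stands, but it does not establish zero.
- **A record may survive.** The draw session is entered in an ODK survey as it happens. Allocation precedes re-consent in {16c}, so 579 most naturally counts draws, although the protocol does not say so. The withdrawal rule does not say that allocation counts are deleted. What is clearly lost is the women's data; the number who left may be recoverable.
- **Withdrawal and suppression apply to both arms.** Controls may leave at any time under the same rule. Only the re-consent prompt is one-sided.
- **Incentives do not point one way.** Controls who leave forfeit the later insurance, but treatment women who leave lose current cover for themselves and their dependents. No direction of differential retention follows from the text.
- **The bias may be trivial.** At 1% refusal it is 0.1 to 0.2 points, and its sign is unknown.
- **Part of the remedy is too late.** Enrolment is closed, the insurance ended on 14 November 2022 and this protocol version is dated 10 March 2023. Women who left at the draw cannot now be followed up.

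These points limit the claim. They do not remove the conflict between the re-consent and withdrawal rules and the stated analysis.

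**Conclusion.** The conflict in the plan is certain; its effect on the result is not known. If any woman declined after the draw or withdrew later, the analysed set falls short of the randomised set, the re-consent exclusion is prompted by allocation in one arm only, and the intention-to-treat analysis, attrition check and least-squares adjustment cannot be carried out as stated. LATE does not repair this.

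Under a null effect, the protocol's 20% STI risk and assumed decliner risks of 10% to 40%, the spurious difference runs from a negligible 0.1 to 0.2 points at 1% refusal to 1.1 to 2.2 points at 10% refusal, in either direction, against a 6-point target. These are illustrations, because the protocol gives neither the number of decliners nor their risk. The point still deserves action now: the missing counts decide whether the trial may call its main analysis intention-to-treat.

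**What to change.** 1. **Withdrawal rule.** Amend it so that data collected up to withdrawal are kept unless the woman asks for erasure, where the consent given and ethics approval allow. In every case keep a de-identified record of allocation and stratum.
2. **Counts.** State whether 579 was counted before or after re-consent. From the ODK draw record, report draws, post-draw refusals and withdrawals by arm and by stratum (commercial or transactional sex).
3. **Analysis.** Give bounds over all women drawn beside the primary estimate. Do not describe the analysis as full intention-to-treat if any randomised woman is missing from it.
4. **Any later re-consent.** Separate declining the insurance from leaving follow-up, and analyse decliners in their allocated arm. With complete follow-up this removes the bias from re-consent. For the current cohort it cannot recover women who left at the draw.

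The cost is one amendment with ethics agreement, a tabulation from records that should already exist, and one sensitivity analysis. The amendment needs care, because suppression is the protocol's stated withdrawal term and women may have been told that it applies. Data already erased stay lost, but the counts and bounds can still be reported if the draw record has been kept.
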